##### rs-fMRI data

The preprocessing of rs-fMRI data will be performed using the Statistical Parametric Mapping (SPM) 12 (Wellcome Trust Centre for Neuroimaging; http://www.fil.ion.ucl.ac.uk/spm) and the Data Processing and Analysis of Brain Imaging (DPABI) toolbox according to the following steps: (1) removal of the first 10 rs-fMRI images to allow for signal stabilization; (2) slice-timing correction; (3) realignment for head motion correction (excluding participants with head motion > 3 mm or head rotation > 3°);(4) normalization of functional images into Montreal Neurological Institute (MNI) space through the DARTEL alignment method and resampling to a voxel size of 3 × 3 × 3 mm^3^; (5) regression of nuisance covariates (including Friston-24 head motion parameters, global mean signals, white matter signals, and cerebrospinal fluid signals); (6) smoothing using a Gaussian kernel with a full width at half maximum (FWHM) of 6 mm; and (7) band-pass filtering (0.01–0.08 Hz) of the time series for each voxel to remove low-frequency drift and high-frequency noise.

The bilateral hippocampi will be selected as seed regions to perform seed-to-voxel RSFC analysis. These regions will be extracted from the Automated Anatomical Labeling (AAL) atlas. FC between each seed region and all other brain voxels (excluding the seed clusters) will be calculated using the DPABI toolbox. The mean time series of the left and right hippocampi will be extracted separately, and Pearson’s correlation coefficients will be calculated between the mean time series of each seed and the time series of all other voxels. The resulting correlation coefficients will then be *z*-normalized using Fisher’s *r*-to-*z* transformation. Finally, an RSFC map for each seed region will be generated for each participant.

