#### Statistical analysis

Statistical analysis will be conducted by an appointed statistician blinded to group allocation using R software (version 4.2.1; R Foundation). Intergroup comparisons of RSFC will be performed using the DAPBI toolbox. Normally distributed continuous variables will be reported as mean±standard deviation, while non-normally distributed data will be reported as median [P25 P75]. A *p*-value of <0.05(two-tailed) will be set as the significance level for all analyses.

The intention-to-Treat (ITT) protocol will be used for the analysis of all outcomes. The ITT population will include all participants who are randomized, regardless of treatment adherence or protocol deviations. The missing value will be handled using multiple imputations.

First, intergroup comparisons of demographic data (such as age, sex, and educational level), illness duration, estimated premorbid intelligence function, and PA will be conducted to examine comparability across the three groups. Categorical data will be analyzed using the χ^2^ test. Normally distributed continuous variables will be tested using one-way analysis of variance (ANOVA), whereas the non-normally distributed data will be analyzed using the Kruskal–Wallis test.

Analysis of covariance (ANCOVA) will be applied to the primary outcome and other cognitive measures, with age, estimated premorbid intelligence ability, and PA as covariates. ANCOVA with age and PA as covariates will be used for clinical measures and brain metabolites. Repeated measures ANOVA will be used to compare differences in hippocampal functional connectivity among the three groups. Age, sex, and years of education will be included as covariates. *Post hoc* analysis will be performed for RSFC with interaction effects. Multiple comparisons for hippocampal functional connectivity will be corrected using cluster-level family-wise error (FWE) correction, with a significance threshold set at a p-value of < 0.05. The χ2 test will be used to compare the rate of AEs and SAEs between the groups. Finally, Spearman correlation analysis will be performed to examine the relationships between cognitive outcome measures and imaging indicators exhibiting intergroup differences.

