Acupuncture is a complex intervention, for which clinical effects are composed of specific and non-specific acupuncture effects. The purpose of including a sham acupuncture control in the acupuncture trial is to investigate the specific acupuncture effect. The combination of sham acupuncture and blinding helps control non-specific acupuncture effects (i.e., placebo effect) (61). Multiple sham acupuncture techniques have been developed and can be roughly divided into categories of penetrating and non-penetrating sham methods (62). Non-penetrating acupuncture at non-acupoints, the method used in this study, is the optimal control among available sham acupuncture techniques in terms of placebo effectiveness as it not only excludes key factors contributing to specific acupuncture effects (e.g., acupoint specificity and needling sensation) but also effectively maintains participant blinding (63). A recent network meta-analysis of 45 randomized controlled trials on chronic pain showed that non-penetrating acupuncture at non-acupoints had the lowest placebo effect compared to manual acupuncture, shallow needling at acupoints, and non-acupoint acupuncture, with 64.8% of the surface under the cumulative ranking curve (SUCRA) (64). The Park sham device is one of the most frequently used non-penetrating sham acupuncture methods in clinical trials (65). Validation studies of Park sham acupuncture have shown excellent blinding effectiveness, especially in combination with non-acupoints (66–68). Furthermore, the blunt needle tip briefly contacts the skin during insertion in practice and does not consistently stimulate the skin during needle retention; thus, the possibility of persistent activation of sensory afferent fibers is low. This sham acupuncture method has been widely used in high-quality acupuncture trials and has successfully revealed the efficacy of acupuncture in the treatment of chronic spontaneous urticaria, Parkinson’s disease-related fatigue, irritable bowel syndrome, and herniated disk-related chronic sciatica (69–72). Therefore, non-penetrating acupuncture at non-acupoints using the Park sham device will be applied in this trial.

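### If verum versus sham connectivity is tested in the clusters that the three-arm interaction selected from the same scans, its false-positive rate there exceeds 5% when waitlist truly differs

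*Protocol article*

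**What the plan says.** Under rs-fMRI data, the outcome is a brain-wide map for each hippocampus: "The bilateral hippocampi will be selected as seed regions to perform seed-to-voxel RSFC analysis", and "FC between each seed region and all other brain voxels (excluding the seed clusters) will be calculated using the DPABI toolbox". No target region is named in advance.

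Under Statistical analysis, four statements govern the comparison:

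- Omnibus test: "Repeated measures ANOVA will be used to compare differences in hippocampal functional connectivity among the three groups".
- Where contrasts follow: post hoc "analysis will be performed for RSFC with interaction effects".
- Multiplicity: connectivity comparisons are "corrected using cluster-level family-wise error (FWE) correction, with a significance threshold set at a p-value of < 0.05".
- General level: a p "value of <0.05(two-tailed) will be set as the significance level for all analyses".

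The article does not say whether the post hoc step uses cluster means, a map restricted to the interaction clusters, or a new whole-brain map. It also does not say whether the FWE sentence covers that step. On the sham arm, the Discussion says: "The purpose of including a sham acupuncture control in the acupuncture trial is to investigate the specific acupuncture effect".

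**The concern.** A significant overall test gives some protection to pairwise tests on one variable fixed in advance. It does not give the same protection when the variable is a cluster found by searching the brain for large group differences in the same data.

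Suppose that verum and sham change connectivity equally and only waitlist differs. Chance verum-sham noise then helps some voxels pass the three-arm test, and a post hoc test in those voxels finds the same noise again. A change shared by both needling arms could be reported as specific to verum, which is the question the sham arm is there to answer. The result could also travel further, because the closing Spearman analysis takes forward the imaging indicators that showed group differences.

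**Working it through.** The article gives no error rate for the post hoc connectivity tests, so there is no figure of its own to reproduce. The check asks how often verum versus sham reaches p < 0.05 when the two are truly equal.

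**Inputs from the article.** Three arms at 1:1:1; two-sided 0.05; cluster-level FWE at 0.05; a search over all voxels for each of two seeds; 3 mm voxels; and "smoothing using a Gaussian kernel with a full width at half maximum (FWHM) of 6 mm".

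**Assumptions, not in the article.** Cluster-forming p of 0.001 or 0.01; final map smoothness of 3 to 4 voxels (9 to 12 mm); waitlist effect absent, or present in a blob of radius 3 or 5 voxels; post hoc test on the cluster mean, with no pairwise adjustment.

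**Step 1: one voxel.** With equal arms, the group-by-time interaction splits into two independent parts: z1 (verum minus sham) and z2 (mean of both needling arms minus waitlist). In large samples a voxel is selected when z1² + z2² > c, with c the chi-square(2) cut-off: 13.816 for p = 0.001 and 9.210 for p = 0.01. With z1 ~ N(0,1) and z2 ~ N(d,1), where d is the waitlist effect in standard errors, the error rate given selection is P(|z1| > 1.96 | z1² + z2² > c). By numerical integration:

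| d | Selected, p 0.001 | Error given selection | Selected, p 0.01 | Error given selection |
|---|---|---|---|---|
| 0 | 0.1% | 67.0% | 1.0% | 59.7% |
| 1 | 0.7% | 33.1% | 4.0% | 28.7% |
| 2 | 6.3% | 16.6% | 20.4% | 13.3% |
| 3 | 28.6% | 9.7% | 55.3% | 7.7% |
| 4 | 66.1% | 6.5% | 86.7% | 5.6% |
| 6 | 99.2% | 5.0% | 99.9% | 5.0% |

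A strong waitlist effect gets the voxel selected whatever z1 is, so no bias remains. A weak effect needs help from z1. The product of the two columns never exceeds 5% (for d = 2 at p 0.001, 0.063 × 0.166 = 1.0%). That is the protection the omnibus test gives to one fixed variable. Any excess per study must come from the search.

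**Step 2: the search.** Smooth 3D fields of 40 × 48 × 40 voxels were simulated with verum equal to sham everywhere and the interaction cluster extent calibrated to 5% FWE. Selected rows, smoothness 3 voxels, 1,200 runs each:

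| Cluster-forming p | Blob radius, effect in SE | Any cluster | Error among selected clusters | Error per study and seed | Separate whole-brain verum-sham map |
|---|---|---|---|---|---|
| 0.001 | none | 3.3% | 71.8% | 2.3% | 4.9% |
| 0.001 | 3, 4 | 49.2% | 14.8% | 7.3% | 4.4% |
| 0.001 | 5, 3 | 81.0% | 19.5% | 16.4% | 5.6% |
| 0.001 | 5, 6 | 100% | 8.2% | 8.2% | 4.8% |
| 0.01 | none | 5.8% | 78.4% | 4.7% | 5.5% |
| 0.01 | 3, 4 | 34.8% | 30.6% | 10.8% | 3.6% |
| 0.01 | 5, 3 | 93.5% | 20.3% | 19.5% | 4.5% |
| 0.01 | 5, 6 | 100% | 11.9% | 12.2% | 4.8% |

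Over all settings run with a waitlist effect:

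- Among selected clusters at cluster-forming p 0.001, the rate was about 8% to 29% for a moderate to strong effect and 33% to 70% for a weak one. At 0.01 it was 12% to 31%.
- Counting only clusters at the true waitlist effect, it was 6% to 24%.
- Per study and seed, it was about 4% to 21%.
- Bonferroni over three pairs still left about 6% to 33% among selected clusters.

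**Step 3: size of effects.** Mean |z| for verum versus sham in selected clusters was about 1.0 to 3.6, against √(2/π) = 0.80 without selection. The needling-versus-waitlist contrast was inflated about 1.1 to 3.1 fold, most when power was low.

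**Step 4: alternatives.** A region fixed in advance gave 4.2% to 7.0%, and a separate whole-brain verum-sham map with its own FWE gave 3.6% to 5.6%. Both are consistent with 5% given simulation error.

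**The case against.** The strongest reply is that the article does not fix the criticised procedure. The sentence directly after the post hoc one applies cluster-level FWE to connectivity comparisons, and group comparisons of connectivity are assigned to the imaging toolbox rather than to R. Both fit voxelwise pairwise maps under the same correction. If those maps are whole-brain, the inflation disappears. A condensed article may also leave the form of the post hoc test and the cluster-forming threshold to a fuller document.

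This stands in part, and it is why the point is conditional. It does not dispose of it. The article itself says where the contrasts are run, ties that to the interaction, and names no separate map. Correcting only within the interaction clusters would leave the selection in place.

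A reader might infer something stronger: that the plan will declare a verum-sham difference some two to six times too often, and that its effect sizes are overstated. The documents do not support that.

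- Such a multiple is a rate among selected clusters, not per study. It needs a real waitlist effect and assumed settings; over the settings tried it ran from about 1 to 17.
- With no effect in any arm, the interaction FWE holds the per-study rate at or below 5% per seed.
- Nowhere does the article say that effect sizes will be estimated from the selected clusters. They would be overstated if they were.

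It is also fair that connectivity is a secondary outcome and the mechanism is described as exploratory. The primary SDMT result is untouched.

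**Conclusion.** The concern holds in conditional form. If verum versus sham is tested at p < 0.05 in interaction-selected clusters, the error rate among those clusters exceeds 5% when waitlist truly differs. That is plausible for an untreated arm that cannot be blinded. The excess runs from almost none with a strong waitlist effect to a rate of 30% or more with a weak one; per study and seed the rate is about 4% to 21%. The direction follows from the structure of the test. The size depends on threshold, smoothness and waitlist effect, all assumed here. The matter deserves correction because verum versus sham is the contrast that carries the claim of a specific effect, but it bears on a secondary imaging outcome only.

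**What to change.** In Statistical analysis, replace the post hoc sentence with a statement that:

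- the verum-sham group-by-time contrast (and verum-waitlist, if it is to be claimed) is tested as its own whole-brain map for each hippocampal seed, with cluster-level FWE correction;
- any claim of a specific verum effect on connectivity rests on that map;
- values extracted from interaction clusters are shown as description only.

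If separate whole-brain maps are already intended, saying so settles the point. The cost is about one sentence and one or two further maps per seed from scans already planned. The downside is a somewhat less sensitive verum-sham test.

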It has been documented that acupuncture therapy treats cognitive impairment by modulating hippocampal connectivity. Functional MRI (fMRI) studies have identified increased RSFC of the hippocampus among patients with Alzheimer’s disease (AD) after 10 min of acupuncture stimulation compared to pre-acupuncture measurements (43, 44). Wei et al. (45) also found that acupuncture treatment significantly enhanced hippocampal RSFC in AD patients, which was accompanied by improvements in general cognitive function. Similarly, Wang et al. reported that acupuncture treatment improved general cognitive function in patients with subjective cognitive decline (SCD) by increasing RSFC of the hippocampus (46). A modulatory effect on cerebral metabolites has also been observed for acupuncture. The findings of ^1^H-MRS research suggested that improvements in general cognitive function, visuospatial skills, and executive function following acupuncture treatment in patients with type 2 diabetes were associated with elevated levels of *γ*-aminobutyric acid (GABA) and NAA in the left basal ganglia, as well as reduced myo-inositol (mI) concentrations in the right basal ganglia (47). Guo et al. (48) revealed that acupuncture-induced cognitive improvements in individuals with chronic partial sleep deprivation-related cognitive dysfunction were correlated with increased levels of NAA and choline (Cho), as well as decreased GABA in the basal ganglia. Moreover, Zeng et al. (49) found that acupuncture treated cognitive dysfunction in patients with gynecological cancer by increasing NAA and Cho levels in the left hippocampus. However, whether acupuncture treatment can improve cognitive function in PCME/CFS patients by modulating hippocampal RSFC and metabolites is unclear.

Accordingly, this multimodal MRI trial is designed to assess the efficacy of acupuncture treatment in improving cognitive function in PCME/CFS patients and to explore whether such improvements occur by modulating hippocampal functional connectivity and metabolism.

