## Methods and analysis

### Study design

This is a prospective, three-armed randomized controlled trial using rs-fMRI and ^1^H-MRS, which will be jointly conducted by two hospitals in Chengdu. A total of 129 patients with ME/CFS occurring after COVID-19 and 30 HCs who have fully recovered from COVID-19 will be recruited. After baseline assessment, eligible patients will be randomly assigned to a verum acupuncture (VA), sham acupuncture (SA), or waitlist control group in a 1:1:1 ratio and will receive an 8-week intervention or wait. Figure 1 shows the flow chart of this trial. This study will be conducted in accordance with the Declaration of Helsinki, the Consolidated Standards of Reporting Trials (CONSORT) guidelines (50), and the Revised Standards for Reporting Interventions in Clinical Trials of Acupuncture (STRICTA) guidelines (51). This protocol has been reviewed and approved by the Ethics Committees of the Affiliated Hospital of Chengdu University of Traditional Chinese Medicine and the Public Health Clinical Center of Chengdu and has been registered at ClinicalTrials.gov (NCT07357688).

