#### Sample size calculation

The PASS software (version 21.0.3) was used to calculate the sample size. Based on two acupuncture trials that used the Symbol Digit Modalities Test (SDMT) as the primary outcome (56, 57), we estimated that the mean and standard deviation of the change in the SDMT score at week 8 after randomization would be 3.75 ± 4.95, 2.45 ± 5.21, and 1.30 ± 4.35 for the VA, SA, and waitlist control groups, respectively. With *α* = 0.05, *β* = 0.2, a power of 0.8, and a two-sided test for group differences, 36 participants are required in each group. Assuming a 20% dropout rate, 43 cases are needed per group, resulting in a total sample size of 129 participants.

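### The imaging–cognition correlation does not adjust for arm; if arms are pooled, arm differences alone can produce a significant result that shows no patient-level link

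*Protocol article*

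**What the plan says.** The last step in the Statistical analysis section of the Protocol article is this: "Spearman correlation analysis will be performed to examine the relationships between cognitive outcome measures and imaging indicators exhibiting intergroup differences". The section applies a p-value of "<0.05(two-tailed) will be set as the significance level for all analyses".

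The same section names covariates for the cognitive measures, the clinical measures, the metabolites and hippocampal connectivity. For the correlation it names none. It mentions no stratification by arm and no partial correlation or mediation model, and it does not say whether the three arms are pooled or taken one at a time.

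The correlation serves the second aim in the Introduction, "to explore whether such improvements occur by modulating hippocampal functional connectivity and metabolism". It is the only analysis described that links imaging to cognition.

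**The concern.** Two features of the plan act together. The selection rule keeps imaging indicators that differ by arm, so the link from arm to imaging is present by construction. The aim is about cognitive improvement under treatment, and the sample-size section assumes such an improvement, so a link from arm to cognition is expected too. When arm shifts both variables, verum patients sit higher on both and waitlist patients lower on both. The pooled data then correlate even if, within each arm, a patient's imaging change says nothing about that patient's cognitive change.

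The group comparisons already show that both variables differ by arm. A correlation that restates this adds nothing on mechanism, yet readers will tend to take it as support for the mechanism aim.

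**Working it through.** **Plan's own figure.** The article states no error rate, power or effect size for the correlation, so there is nothing to reproduce. The sample-size section serves only as a source of inputs.

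**Inputs from the article.**
- Mean ± SD of SDMT change "would be 3.75 ± 4.95, 2.45 ± 5.21, and 1.30 ± 4.35 for the VA, SA, and waitlist control groups, respectively" (Sample size calculation).
- Size per arm: "36 participants are required in each group", and "Assuming a 20% dropout rate, 43 cases are needed per group". This gives 3 × 36 = 108 evaluable and 3 × 43 = 129 randomised.
- Two-sided 5% level (Statistical analysis).

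**Inputs assumed here.**
- The imaging change has SD 1 within each arm and arm means d, d/2 and 0 for verum, sham and waitlist. The documents give no value for d, so it is varied from 0.3 to 1.5.
- Imaging and cognition are unrelated within every arm.
- Indicators are kept if a one-way ANOVA across arms gives p < 0.05.

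**Step 1: the correlation created by arm alone.**
- Mean SDMT change over arms: (3.75 + 2.45 + 1.30)/3 = 2.50. Deviations: +1.25, −0.05, −1.20.
- Imaging deviations: +d/2, 0, −d/2.
- Between-arm covariance: (1.25·d/2 + 1.20·d/2)/3 = 2.45d/6 = 0.408d.
- SDMT variance: within arms (24.50 + 27.14 + 18.92)/3 = 23.52; between arms (1.5625 + 0.0025 + 1.44)/3 = 1.00; total 24.52, so SD 4.952.
- Imaging variance: 1 + d²/6.
- Induced correlation: r = 0.408d / (4.952·√(1 + d²/6)).

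For d = 1.0, r = 0.408/(4.952 × 1.080) = 0.076. For d = 0.3, r = 0.1225/(4.952 × 1.0075) = 0.025. For d = 1.5, r = 0.6125/(4.952 × 1.173) = 0.105.

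**Step 2: what this does to the test.** With N = 129 the test statistic shifts by about r·√(N − 3) = r·√126. For d = 1.0 the shift is 0.076 × 11.22 ≈ 0.86. The rejection probability is then P(Z > 1.10) + P(Z < −2.82) ≈ 0.135 + 0.002 ≈ 0.14. For d = 0.3 the shift is about 0.28 and the probability is about 0.06, before any selection. Selection raises this at small d, because the trials that pass are those with the larger observed imaging differences.

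**Step 3: simulation with the selection rule.** Pooled Spearman, 43 per arm, zero within-arm association:

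| Assumed imaging effect d (SD) | Significant, imaging selected | Significant, cognition also differs by arm (p < 0.05) |
|---|---|---|
| 0.3 | 7.7% | 8.8% |
| 0.5 | 8.1% | 11.1% |
| 0.8 | 11.2% | 14.6% |
| 1.0 | 13.5% | 19.2% |
| 1.5 | 22% | 32% |

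Separate runs agree to within about one percentage point. At 36 per arm and d = 1.5 the two rates are about 20% and 31%.

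**Step 4: two controls.**
- A rank correlation with arm means removed rejects in 4.6–5.8% of selected cases in every scenario.
- If the cognitive measure has no arm effect, the pooled Spearman stays at 4.4–5.6% even after imaging selection. Both variables must be shifted for the problem to arise.

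**The case against.** The strongest reply is that the article never says the arms are pooled. Correlations within each arm fit the sentence too and are free of the problem, and a condensed article may leave that detail to a fuller plan. This stands in part: pooling must not be reported as what the plan says. It does not remove the point. The article fixes a method and a selection rule, lists covariates for the other outcome models and none for this one, and a plain Spearman coefficient adjusts for nothing.

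Second, if treatment shifts both variables, the marginal association is real and a rejection is no error in the narrow sense. This stands. The rates above count as errors only for a within-arm or mechanistic reading. That is, however, the reading that the aim invites.

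Third, the aim is exploratory, and nothing in the article makes a significant correlation the criterion for concluding mechanism. This also stands, and it lowers the priority of the point.

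Fourth, an arm-adjusted correlation does not prove mechanism either, since a within-arm association can be confounded. True, but it at least tests something that the group comparisons have not already shown.

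**Conclusion.** The concern holds in conditional form. If arms are pooled and treatment shifts both variables, about 7–14% of selected indicators would correlate significantly without any within-arm link, for assumed imaging effects of 0.3–1.0 SD. The range is about 9–19% if the cognitive measure also differs by arm, and about 20% or more at 1.5 SD. Among selected indicators the mean spurious rho is small, about 0.05–0.1. These figures rest on the article's SDMT means and SDs, on imaging effects that are assumed, and on zero within-arm association.

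A reader might infer three stronger things that the documents do not support:
- **That the plan carries two to four times the nominal false-positive rate.** No imaging effect size is given. For SDMT with imaging selection alone, the ratio is 1.4–1.8 at 0.3–0.6 SD and reaches 2 only at about 0.8 SD. That is larger than the 0.53 SD verum–waitlist difference implied for SDMT itself (2.45/4.66, with 4.66 = √((4.95² + 4.35²)/2)).
- **That choosing indicators because they differ by arm inflates the error by itself.** It does not; an arm effect on cognition is needed as well. The SDMT-based rates therefore cannot be carried over to the other cognitive tests, for which no arm effect is assumed.
- **That the article stakes a mechanism claim on this test.** It says only that it will explore the question.

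**What to change.** Replace the closing sentence with one that specifies a partial Spearman correlation between baseline-to-week-8 changes in the cognitive measure and in the imaging indicator, adjusted for randomised arm by two indicator variables. Within-arm correlations combined across the three arms would serve equally well. Add that any unadjusted pooled correlation is descriptive only.

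The cost is one sentence of wording and two degrees of freedom out of 129 patients (108 if only the evaluable number remains). No new data are needed.
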